#### Sample Size

A conservative approach was adopted for this feasibility study, which emphasizes descriptive and qualitative feedback. Consequently, based on the recommendations for pilot studies (44), we plan to include 80 participants (40 cases, 40 controls) over a 2-year inclusion period. As there are around 280 inpatient admissions per year in the Department of Child and Adolescent Psychiatry, i.e., *n* = 560 potential participants contacted at baseline during the 2 years, this will represent a 14% inclusion rate. We predict that the prevalence of SUDs will be similar to that previously reported (18). A good level of compliance with EMA and Stop-Cannabis is expected, consistent with previous studies that reported high levels of adherence (up to 80%) to similar tools in adolescents with comorbid psychiatric disorders (31, 45), and in adults with associated severe psychiatric disorders (32, 46). An acceptance rate of 80% is expected in the SUD group and 50% for the control group. A 50% retention rate at 1-year follow-up is anticipated based on previous longitudinal studies among adolescents (47). In case of a lower enrollment rate, we will either continue to enroll participants during an additional year (2019) in order to reach the intended sample size or use incentives (e.g., free participation in leisure and sport activities in groups) to encourage participant enrollment.

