### EMA and Stop-Cannabis App Tools

#### Ecological Momentary Assessment

The EMA was designed as an app for mobile phones. This application allows several daily self-assessments (e.g., five times a day for 2 weeks at different times of the study/monthly). Data are collected in response to a signal from the EMA app that occurs at various times of the day. The app has been programed to send signals (i) a fixed number of times per day at predetermined times (e.g., at bedtime) and (ii) at random (with a balance between week, weekends, and holidays, with different time intervals in daytime). Participants are also asked to complete self-assessment immediately following substance use.

The same questions are presented regardless of assessment type. There are seven questions in total:
Information relating to substance use:
○Daily use of each substance in list.○Level of withdrawal symptoms during participants’ most recent period of abstinence from 0 (not at all) to 5 (severe).○Level of craving from 0 (no urge) to 5 (extreme urge).Information relating to psychopathology:
○Level of negative affect rate using a brief version of the Positive and Negative momentary Affect Scale (PANAS) (48) adapted for EMA (32). Participants provide ratings of the extent to which they felt each emotion on a 1–5 point Likert-type scale.○Main psychiatric symptoms.Information relating to environment:
○Stressful events.○Activities: physical activity, planned activity, lone activity, social activity with peers, family activity, and online activity.

Participants will be trained on EMA use during the week prior to hospital discharge. They will be asked to respond to any signals within 1 h if possible. Consistent with other EMA protocols, participants will complete 2 days of practice data (not used for analyses), after which they will receive feedback on adequate use and compliance. Participants will then be invited to complete EMA assessments for 2 weeks, as this timeframe appears sufficient to monitor substance use (45). To limit attrition, participants will be paid 30€ for completing the baseline assessment and 10€ for each week of complete EMA data, up to a maximum possible payment of 60€ over 1 year.

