##### Secondary Outcomes

(1)The number of inpatients with SUDs will be compared with the total number of adolescents admitted to the Department during the inclusion period.(2)Descriptive analyses of clinical and psychosocial variables will be conducted. Chi-square will be used to compare categorical variables, and Student’s *t*-test for continuous variables. A difference of *p* < 0.05 will be considered statistically significant.(3)Univariate logistic regression analyses will be performed to determine whether clinical features (as independent variables) predict the onset of SUDs at 1 year (as dependent variable) in the non-SUD control group and persistence or cessation in the SUD group. Possible mediators of this relation will be examined using the four-step approach proposed by Baron and Kenny (65), followed by a Sobel–Goodman test. In particular, we will test the mediation effect of the baseline impulsivity score, the baseline level of sensation-seeking (subscales of the UPPS-P score), and the baseline level of mood lability (ARI total score) on the relationship between psychopathology and SUDs.(4)Comparable analyses would be conducted to determine the clinical and psychosocial risk factors for the persistence of SUDs among those with non-cannabis substance use at baseline.(5)Specific analyses based on mixed-effect models (a random effect for participants and fixed effects for time) will be performed to examine the interplay between the pattern of substance use, psychiatric symptoms, and contextual stressors for treating EMA data [as in Ref. (45, 66)]. In line with previous recommendations, data will be studied at the daily level (with average ratings), at the concurrent momentary level, and at the prospective level using both linear and non-linear modeling (32). These analyses will be performed and presented separately between those with cannabis use disorder and the other participants to prevent any interference due to the use of the Stop-Cannabis app.(6)Correlational analyses will be carried out to examine the association between the level of app use (EMA or Stop-Cannabis) (i.e., mean percentage of random prompts, mean percentage of days assessment completed) and participant’s clinical outcome at follow-up (i.e., frequency of substance use and level of functional impairment at 1 year).

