#### Secondary Objectives

This study will measure the prevalence and the characteristics associated with the presence of SUDs in a sample of adolescents hospitalized in a psychiatric setting. Findings are expected to be in a similar range as those previously reported by Daudin et al. (18). We will then examine the possible relationship between SUDs and specific psychosocial and clinical features of inpatient adolescents. We expect this study to confirm that both internalized and externalized disorders are significantly associated with SUDs and that the presence of SUDs is associated with a higher level of impulsivity, mood dysregulation/borderline traits, and sensation-seeking traits (68–70). We predict that a bidirectional positive relationship between the level of substance use and the severity of other psychiatric symptoms will be noted at a daily level, and – if confirmed – that this association would be strengthened in a context of interpersonal relationship (with family and with peers) compared to other situations. A significant negative association between the level of the Stop-Cannabis app use and the participant’s clinical outcome at follow-up is expected. Such additional exploratory analysis would provide preliminary information about the possible benefit of the app in naturalistic settings.

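### The EMA models name one participant random effect: if symptom–use slopes differ between adolescents the slope's standard error is understated, and the within/between split is left open

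*Protocol article*

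**What the plan says.** In the protocol article, Statistical Methods, Secondary Outcomes, item (5), the model is given as follows: "Specific analyses based on mixed-effect models (a random effect for participants and fixed effects for time) will be performed". Its purpose is "to examine the interplay between the pattern of substance use, psychiatric symptoms, and contextual stressors for treating EMA data". Three levels of analysis are named: "data will be studied at the daily level (with average ratings), at the concurrent momentary level, and at the prospective level". The analyses are to be "performed and presented separately between those with cannabis use disorder and the other participants".

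No random slope and no residual correlation structure is named. Nothing is said about whether time-varying predictors are centred or split into within- and between-person parts. Two cited studies are given as models for the method, and a third for the levels of analysis.

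Under Anticipated Results, Secondary Objectives, the authors state what they expect to find: "a bidirectional positive relationship between the level of substance use and the severity of other psychiatric symptoms will be noted at a daily level". Clinical and Research Implications presents EMA as the means of seeing the sequence of use, context and symptoms, in a sample described as diagnostically broad and more severe than those of earlier EMA projects.

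Under Sample Size, "we plan to include 80 participants (40 cases, 40 controls) over a 2-year inclusion period"; controls have no EMA, so at most 40 participants contribute, before the split by cannabis use disorder. The prompting schedule is given as an example: "five times a day for 2 weeks at different times of the study/monthly".

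**The concern.** The question is whether, within an adolescent, symptoms and stressors accompany or precede substance use. That is a within-person slope. A single participant random effect, read as an intercept, lets adolescents differ in their level of use but gives them all the same slope. When true slopes differ, the participants are the sampling units for the average slope. A model with a common slope instead counts every prompt as independent information about it. The standard error is then too small, and the shortfall grows with the number of prompts per person.

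A separate issue is what the slope estimates. If a predictor enters uncentred, its coefficient mixes the within-person effect with the between-person one (more symptomatic youths use more). Whether that happens here is not stated.

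At stake is the credibility of the interplay findings: understated standard errors make the predicted positive relationship easier to confirm by chance.

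**Working it through.** The document gives no power, variance or standard error for these models, so there is no planned figure to reproduce.

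**Inputs from the document**
- Prompts per two-week burst: 5 × 14 = 70 (given as an example).
- Expected completion: above 70% of random signals (Anticipated Results, Primary Objectives). Applied to all prompts (assumption): 0.70 × 70 = 49 records.
- The same section expects 50% of end-of-day assessments. If one of the five daily prompts is at bedtime (assumption): 56 × 0.70 + 14 × 0.50 = 46.2, a minor change.
- Daily level: 14 daily averages per two-week burst.
- EMA participants: at most 40.

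**Assumptions**
- Residual SD 1 and within-person predictor SD 1 at each level; slope SD τ from 0 to 0.3.

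**1. Standard error with a common slope**
- Model SE = √(1/(N·T)).
- True SE = √(1/(N·T) + τ²/N).
- Ratio true/model = √(1 + T·τ²).
- Type I error = 2Φ(−1.96/ratio).

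Example: N = 40, T = 49, τ = 0.2. Model SE = √(1/1960) = 0.0226; true SE = √(0.00051 + 0.00100) = 0.0389; ratio = √2.96 = 1.72; type I error = 25.5%.

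| τ | T = 49: ratio | T = 49: type I | T = 14: ratio | T = 14: type I |
|---|---|---|---|---|
| 0 | 1.00 | 5.0% | 1.00 | 5.0% |
| 0.1 | 1.22 | 10.8% | 1.07 | 6.6% |
| 0.2 | 1.72 | 25.5% | 1.25 | 11.7% |
| 0.3 | 2.33 | 39.9% | 1.50 | 19.2% |

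At τ = 0.05 and T = 49 the ratio is √1.1225 = 1.06 and the type I error about 6%. The fitted residual variance absorbs some slope variance (1 + τ²), which lowers the top figure slightly: at T = 49 and τ = 0.3, √(5.41/1.09) = 2.23, or about 38%.

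N cancels from the ratio. At T = 49 and τ = 0.2, the model and true SEs are 0.0270 and 0.0464 for N = 28, and 0.0412 and 0.0710 for N = 12: the same 1.72.

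**2. Simulation check** (150 data sets per setting, random-intercept model, N = 40; some fits raised convergence warnings)
- T = 49, τ = 0, no serial correlation: empirical SE 0.0207, model SE 0.0223, coverage 95%.
- T = 49, τ = 0.2: empirical SE 0.0407, model SE 0.0227, coverage 69%.
- Same, with person-mean centring: coverage 77%. The closed form implies 100 − 25.5 = 74.5%. The simulation error is about √(0.69 × 0.31/150) = 3.8 points, so the two results agree with it, and centring alone does not repair the SE.
- T = 14, τ = 0.2: coverage 85%.
- T = 49, τ = 0, AR(1) correlation 0.5 in predictor and residual: coverage 85%.

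**3. Leakage, if predictors were uncentred**
- With random-intercept variance σu² and residual variance σ² = 1, let ψ = 1/(1 + T·σu²). The weight on the between-person slope is ψB/(W + ψB), where B is the variance of the person means and W the within-person variance.
- Example: T = 14, outcome and predictor ICC both 0.3. σu² = 0.3/0.7 = 0.429; ψ = 1/7 = 0.143; B = 0.429 + 1/14 = 0.50; W = 13/14 = 0.929; weight = 0.0714/(0.929 + 0.0714) = 7.1%.
- Over outcome ICC 0.2 to 0.5 and predictor ICC 0.3 to 0.7: 0.9% to 15.4% at T = 49, and 3.5% to 36.5% at T = 14.
- Simulated, between-person slope 0.5 and within-person slope 0: bias 0.016 and coverage 89% at T = 49; bias 0.045 and coverage 83% at T = 14, where the model SE is 0.043. With centring at T = 49: bias 0.000, coverage 95%.

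**The case against.** The article condenses a fuller protocol and refers to earlier studies for method. It also announces linear and non-linear modelling, and the Figure 3 note lists hierarchical linear modelling, which can carry random slopes. A parenthesis that mentions a random effect does not say intercept only. Every slope SD used here is assumed, and small values do little harm. The item is exploratory in a pilot study, and the p < 0.05 rule is written under item (2), not item (5).

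Much of this stands, and it rules out several stronger readings that a reader might infer:
- **That predictors are uncentred.** The text is silent, so leakage can only be stated as a condition.
- **That the intervals are necessarily too narrow.** With neither slope variation nor serial correlation, coverage was 95%.
- **That the small subgroups cause the inflation.** N cancels from the ratio; the number of records per person drives it.
- **That the largest figures apply to the predicted daily relationship.** At the daily level they are 6.6% to 19.2%; the higher ones belong to the momentary level.

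What does not stand is the view that there is nothing to correct. The parenthesis does describe the random part of the model, in the singular, and a random intercept is what most analysts would fit from it. A common slope is hard to defend in so mixed a sample.

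**Conclusion.** The point holds in conditional form. The model as written, on its ordinary reading, understates the standard error of the symptom–use slope if slopes vary between adolescents, and also in the simulated case where both predictor and residual are serially correlated. For slope SD 0.1 to 0.3, type I error is about 11% to 40% at 49 momentary records and about 7% to 19% at 14 daily records. These figures rest on unit residual and predictor SDs, one two-week burst and 70% completion of all prompts; the document gives no slope variance. Pooling several bursts would raise T and hence the ratio.

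The leakage part is a request for clarification, with a consequence mainly at the daily level if predictors turn out to be uncentred. Because the analysis is secondary and exploratory, the priority is modest.

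**What to change.** In Statistical Methods, Secondary Outcomes, item (5):
- Add a participant-level random slope for each focal time-varying predictor.
- Enter each such predictor as its deviation from the person mean, plus the person mean as a separate term.
- Allow for serial correlation of residuals, for example AR(1).
- In prospective models, do not person-mean-centre a lagged outcome. In short series this biases its coefficient: a true 0.30 was estimated at 0.15 with 10 records and 0.20 with 14. An uncentred lag is itself correlated with the random intercept, so report results with and without it as a sensitivity analysis.
- If the random slope does not converge, use a small-sample-corrected cluster-robust interval. A participant bootstrap is an alternative but stays somewhat liberal in small subgroups: with slope SD 0.2 and 10 records, a percentile interval gave type I error of 10% at 12 participants and 7.5% at 24.

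The cost is analysis wording only; data collection is unchanged. Intervals widen: at N = 40 and T = 49 the standard error becomes 0.028, 0.039 or 0.053 for slope SD 0.1, 0.2 or 0.3, against 0.023 from the common-slope model. Occasional non-convergence is likely in the smaller subgroup.

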## Abstract

**Context:**

Substance use disorders (SUDs) are highly prevalent among inpatient adolescents with psychiatric disorders. In this population, substance use and other psychiatric outcomes can reinforce one another. Despite the need for integrated interventions in youths with dual diagnoses, few specific instruments are available. App-based technologies have shown promising results to help reduce substance use in adolescents, but their applicability in youths with associated severe psychiatric disorders is poorly documented. We aim to evaluate the feasibility of an ecological momentary assessment (EMA) intervention for all substance users, and of a smartphone application for cannabis users (Stop-Cannabis), for outpatient treatment after hospital discharge.

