**Methods and analysis:**

All inpatient adolescents with psychiatric disorders hospitalized between 2016 and 2018 in a university hospital will be systematically screened for SUD and, if positive, will be assessed by an independent specialist addiction team. Participants with confirmed SUDs will be invited and helped to download an EMA app and, if required, the Stop-Cannabis app, the week preceding hospital discharge. Information about the acceptability and use of both apps and the validity of EMA data in comparison to clinical assessments will be assessed after 6 months and 1 year.

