## Methods and Analysis

### Selection of Participants

#### Inclusion and Exclusion Criteria

Participants will be adolescents (11–18 years old) who are hospitalized in the Department of Child and Adolescent Psychiatry at the Pitié-Salpêtrière University Hospital between September 2016 and September 2018. The participants will be assessed at baseline. According to the presence or absence of comorbid SUDs, they will be included in either the SUDs group or the control group. The SUDs group will receive the mobile apps, whereas the control group will not. Exclusive tobacco consumption is not considered to be a criterion for inclusion in the SUDs group. Inclusion to the non-SUD control group will be made according to a match with adolescents from the SUDs group (for age, gender, inpatient unit, and time of admission). Exclusion criteria include non-French speaking, those without a personal mobile phone, lack of informed consent from parents or from the adolescents, and any mental or physical problems that interfere with participation in the study (e.g., autism with very low communication abilities, severe to profound intellectual disability, severe motor disability).

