**Ecological momentary intervention “Stop-Cannabis.”**
*Notes*: screenshots of the welcome page, the Feedback page, and the main screen with the benefits of change. Adapted from: Monney et al. (39).

The app will automatically monitor the number of times each participant opens the app and records the number of times participants looked at or used each element. A Unique Device Identifier (UDI) is used to connect the participants’ device to the study database and will be replaced in the data set with a random ID for anonymity. After study completion, the UDIs will be automatically deleted from users’ devices. The app will be available for participants in the intervention group for 12 months. After this period, the app will automatically stop data collection. However, participants are free to use the app for as long as they want.

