##### Secondary Outcomes

(1)The prevalence of SUDs among adolescent inpatients will be assessed.(2)The clinical and psychosocial characteristics of participants with and without SUDs at baseline, including history of adverse childhood experiences, comorbid psychiatric diagnoses, and the level of functional impairment, will be compared.(3)The risk of developing SUDs among non-SUD adolescents during a 1-year follow-up period following hospital discharge will be investigated.(4)The proportion of inpatient adolescents with non-cannabis substance use at baseline whose SUDs persist at 1 year will be estimated.(5)We will explore how psychiatric symptoms could affect the pattern of substance use among SUDs participants.(6)We will assess whether specific patterns of Stop-Cannabis app use is associated with substance use outcomes at 1-year follow-up.

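### The EMA models are split by cannabis use disorder to keep Stop-Cannabis out of one stratum, but the text does not limit the app to participants with that diagnosis

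*Protocol article*

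**What the plan says.** All references are to the Protocol article. Statistical Methods, Secondary Outcomes (5), plans mixed-effect models of the EMA data, to be run and presented "separately between those with cannabis use disorder and the other participants to prevent any interference due to the use of the Stop-Cannabis app".

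Who is given Stop-Cannabis is described in several places:

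- Abstract, Context: the study evaluates EMA for all substance users "and of a smartphone application for cannabis users (Stop-Cannabis), for outpatient treatment after hospital discharge".
- Abstract, Methods and analysis: participants with confirmed SUDs "will be invited and helped to download an EMA app and, if required, the Stop-Cannabis app, the week preceding hospital discharge". The need that triggers the second app is not defined.
- Inclusion and Exclusion Criteria: "The SUDs group will receive the mobile apps, whereas the control group will not".
- The Stop-Cannabis App, text after Figure 1: "The app will be available for participants in the intervention group for 12 months". The shown text does not define that group.
- Limitations: the missing comparison group for the app is described as people with cannabis use disorders who do not get it.

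On a related point, Outcomes, Secondary Outcomes (4), reads: "The proportion of inpatient adolescents with non-cannabis substance use at baseline whose SUDs persist at 1 year will be estimated". Objectives, secondary objective (4), names the target as persistence of non-cannabis SUDs.

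**The concern.** The split has a stated purpose: one stratum should show how substance use, symptoms and stressors interact without the influence of an intervention app. A diagnosis serves that purpose only if having the app implies having the diagnosis. If app users can sit in the other stratum, its estimates mix participants with and without the intervention, and a reader told that interference was prevented would be misled. The persistence analysis in (4) raises a smaller version of the same question, because someone with a non-cannabis disorder may also have a cannabis disorder and therefore the app.

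**Working it through.** **Step 1: can a case lack cannabis use disorder?** Yes. The inclusion criteria keep out only one pattern: "Exclusive tobacco consumption is not considered to be a criterion for inclusion in the SUDs group". Alcohol or other SUDs qualify.

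**Step 2: does the protocol separate cannabis use from the disorder?** Yes. Under Screening, cannabis use at least monthly, or a positive urine test, makes a patient screen positive. Under Assessment to Determine Eligibility, a disorder requires a later DSM-5 diagnosis by the addiction unit. Someone can therefore use cannabis, have a confirmed alcohol use disorder, and not have cannabis use disorder.

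**Step 3: where does that participant go?**

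| Statement | Given the app? | Stratum in (5) |
|---|---|---|
| Abstract, Context | Yes | Other participants |
| Abstract, Methods and analysis | Undetermined | Other participants |
| Inclusion criteria, read literally | Yes | Other participants |
| Limitations | Suggests those with the disorder get it; does not say only they do | Other participants |

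No statement rules the participant out of receiving the app.

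**Step 4: size of the stratum.** The plan gives no figure for app recipients. Its recruitment figure reproduces: 2 × 280 = 560 admissions and 80/560 = 14.3%, stated as 14%. The 80 comprise 40 cases. The Introduction cites about 70% with cannabis SUD in an earlier French inpatient study, and Sample Size expects similar prevalence.

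- If 70% applies to cases: 40 × 0.70 = 28 with the disorder and 40 − 28 = 12 others.
- At assumed shares of 60% and 80%: 24 and 16, or 32 and 8.
- If 70% refers to all inpatients and a proportion P of them have a SUD, the share among cases is 0.70/P, which is at least 0.70. Then 12 is an upper bound.
- With the anticipated 50% retention at 1 year: 12 × 0.50 = 6 others remain.

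**Step 5: how many of the 12 could have the app?** Let q be the share of the others who use cannabis below the diagnostic threshold and are given the app. The documents do not give q, so it may lie anywhere from 0 to 1. The expected number is 12 × q, and the chance of at least one, taking participants as independent, is 1 − (1 − q)^12.

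| q (assumed) | Expected number of 12 | Chance of at least one |
|---|---|---|
| 0.10 | 1.2 | 0.72 |
| 0.25 | 3 | 0.97 |
| 0.50 | 6 | >0.99 |

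**Step 6: analysis (4).** The Introduction also cites about 60% with alcohol SUD. If both percentages share one denominator, at least 70 + 60 − 100 = 30% have both, so at least 30/60 = half of those with an alcohol SUD also have a cannabis SUD. Applied to 40 cases, that is at least 12 of 24. Whether they belong in (4) depends on whether non-cannabis use means use of other substances or absence of cannabis use. The text does not settle this.

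**The case against.** The other side has a good deal to say. The Limitations section does point to cannabis use disorder as the app's target, which is the group used in (5), and the reason given for the split suggests that the authors had this in mind. That stands as evidence of intent. It supports the reading that those with the disorder get the app; it does not say that only they do.

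A reader might infer that every statement conflicts with the split. That goes too far: the Methods and analysis paragraph of the Abstract leaves its criterion undefined, which is not a conflict.

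A reader might also infer from the inclusion criteria that all 12 others would have the app. That requires one sentence to be read in isolation. Its evident job is to contrast cases with controls, and the Abstract divides the two apps between all substance users and cannabis users.

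For (4), a reader might infer that the outcome is undefined. It is not, since the secondary objective already names persistence of non-cannabis SUDs. What remains is that the outcome and analysis wording does not follow it closely, and that the handling of participants with both disorders is open.

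Finally, the flow chart is not shown and the article condenses a fuller protocol, so an operational rule may exist there. That could settle the intent, but it would not align the printed statements.

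**Conclusion.** The concern holds in a limited form. The split by cannabis use disorder does not secure its stated purpose, because the text leaves room for a participant without the disorder to be given Stop-Cannabis. The number affected cannot be derived from the documents; the counts for q of 10%, 25% and 50% are illustrations. What can be said is that the stratum is small, about 12 of 40 if the 70% figure applies to cases and fewer if it refers to all inpatients, so even one to three app users would be a visible share. The consequence is confined to secondary, exploratory analyses in a pilot study. The plan sizes no sample and controls no error rate on this split, and the Limitations section already disclaims conclusions about the app's benefit.

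**What to change.** 1. Reconcile the Abstract (both paragraphs), Inclusion and Exclusion Criteria, the availability statement under The Stop-Cannabis App, Secondary Outcomes (5) and Limitations into one statement of who is given Stop-Cannabis. Which rule applies is for the sponsor to decide.
2. In Statistical Methods, Secondary Outcomes (5), split by whether the participant was provided with Stop-Cannabis at discharge, in place of the diagnosis. The stratum without the app then contains no study-provided users by construction. If the sponsor's rule turns out to be that all those with the disorder, and only those, are given the app, this is the same split as the one now planned.
3. Do not split on whether the app was opened. Opening it is self-selected behaviour after baseline and would bring selection into the comparison.
4. As a minor point, align Secondary Outcomes (4), in both the Outcomes and Statistical Methods sections, with secondary objective (4), so that the outcome is persistence of the non-cannabis SUD. Say whether participants who also have a cannabis disorder, and so may have the app, are included.

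The cost is wording and a record of who was given the app. The downside is that strata defined by provision may be less balanced in size than strata defined by diagnosis.
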